### Statistical Analysis

#### Sample Size Estimation

Sensitivity and specificity are used to determine performance, since both are essential in the characterization of diagnostic effectiveness of the BRAINBox TBI Test.

The following assumptions were used to calculate sample size for the primary endpoint (within 96 h of injury) with the blood specimens collected at the first-time point: a one-sample binomial test, a clinical sensitivity of 0.85 and specificity of 0.75, a “difference to detect” of 0.07, alpha of 0.05 and a power of 0.80. The assumptions for sensitivity and specificity are based on findings from HeadSMART pilot trial (30).

The sample size is based on the binomial test for a one sample design using a two-sided significance level of α = 0.05 and a power of 1-β = 0.80 (30). The following hypothesis will be tested:

$$H_{01}:Se=Se_{0}and\;H_{02}:Sp=Sp_{0}(null\;hypotheses)$$

$$H_{\text{a1}}:Se\neq Se_{0}\;and\;H_{\text{a2}}:Sp\neq Sp_{0}(alternative\;hypothesis)$$

Where *Se* (sensitivity) is the proportion of target condition positive subjects that yield a positive test result, *Sp* (specificity) is the proportion of target condition absent subjects that yield a negative test result, Se_0_ is the desired sensitivity and Sp_0_ is the desired specificity.

Generically for both sensitivity and specificity, let p_0_ represent the null value, p_1_ the alternative and let *n* and *m* represent the sample size and the number of observed outcomes of interest, respectively. Based on the binomial distribution, the sample size may be calculated using a numerical approach by solving two equations simultaneously. For a given two-sided significance level α (Type I error), there exists a critical value *c* (nonnegative integer), such that:

$$\sum_{i=c}^{n}\left(\begin{array}{c} n\\ i \end{array}\right)p_{0}^{i}{\left(1-p_{0}\right)}^{n-i}\leq 1-\alpha /2$$

and

$$\sum_{i=c}^{n}\left(\begin{array}{c} n\\ i \end{array}\right)p_{1}^{i}{\left(1-p_{1}\right)}^{n-i}\leq 1-\beta$$

If m ≥ c, then the null hypothesis is rejected at α significance level. There exists the smallest sample size *N*, such that as long as *n* ≥ N, the power is always greater than or equal to 1-β. Then, *N* is the sample size from exact binomial testing.

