### Diagnosis of ATE

Prior to algorithm development, data will be divided into training and validation sets, with a model being derived using the training data. The training phase will include examination of potentially confounding and interacting variables (e.g., age, sex, time from injury until blood draw). Any confounding variables will be included as covariates in the model. Variables with insignificant interaction, as determined by backward selection, will be omitted. The model will provide a probability/score that a subject has ATE. The c-statistic will be reported, and a threshold selected to ensure the model meets the minimum sensitivity and specificity of 85 and 75%, respectively, with confidence intervals, positive predictive value and negative predictive value reported. Accuracy will be reported as the percentage of all suspected TBI subjects correctly classified as “ATE,” vs. “no ATE,” using the identified threshold. Validation data will be derived in an independent subject set (validation cohort), against which the developed model will be tested for generalizability. *P*-values comparing the AUC, sensitivity, specificity, and accuracy will be reported, with alpha defined as < 0.05. Sample size calculation was performed in PASS statistical software (32) using an assumed prevalence of 50% ATE in the subjects enrolled with blunt head injury. The final number of evaluable subjects for the “ATE,” and “no ATE” cohorts, should each not exceed 240, which makes the total number of evaluable subjects 480. An equal number of subjects are needed for algorithm validation (*n* = 480).

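### At 240 subjects per class, specificity falls short of the stated 80% power, and power to meet both the sensitivity and specificity criteria is about 52% or 66%

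*Protocol article*

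**What the plan says.** Under Sample Size Estimation, the protocol article reports both sensitivity and specificity, "since both are essential in the characterization of diagnostic effectiveness of the BRAINBox TBI Test". The inputs for the primary endpoint are "a one-sample binomial test, a clinical sensitivity of 0.85 and specificity of 0.75, a “difference to detect” of 0.07, alpha of 0.05 and a power" set at 80%, and the next paragraph repeats the test "using a two-sided significance level of α = 0.05 and a power of 1-β = 0.80". Two null hypotheses follow, one for each measure, and a generic formula is then given for a single proportion. The direction of the 0.07 difference is not stated. The values 0.85 and 0.75 appear both as assumptions taken from the pilot and as the desired values in the null hypotheses.

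Under Diagnosis of ATE, one cut-off is chosen so that the model "meets the minimum sensitivity and specificity of 85 and 75%, respectively". Algorithm Training and Testing says the same. The evaluable ATE and no-ATE cohorts "should each not exceed 240, which makes the total number of evaluable subjects 480", and an equal number is set for validation.

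Under Prognosis of ATE, 786 blunt head trauma subjects are planned for validation, and the closing text allows the diagnostic and prognostic validation phases to share subjects.

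**The concern.** One power figure is attached to an endpoint that has two hypotheses. A reader will take 0.80 as the chance that a test with the assumed performance passes validation. It can carry that meaning only if each measure is adequately powered at 240 and the power for the pair has been worked out. The article does neither.

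At stake is the size of the diagnostic validation set. If both criteria must be met, a test that truly performs at the assumed alternative would miss at least one of them in a third to a half of validation studies (1 − 0.663 = 0.337; 1 − 0.516 = 0.484), where the printed figure suggests one in five.

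**Working it through.** **Inputs.** From Sample Size Estimation: one-sample exact binomial test, two-sided α = 0.05, power 0.80, difference 0.07, sensitivity 0.85, specificity 0.75. From Diagnosis of ATE: n = 240 per class. The exact test is read in the usual way, with at most 0.025 in each tail under the null.

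**Formula.** For null p0, alternative p1 and size n, c is the smallest count with P(X ≥ c | n, p0) ≤ 0.025. Power is P(X ≥ c | n, p1); the opposite tail adds a negligible amount. For a downward difference, use the lower tail.

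**Reproducing the plan's figure.** The first n to reach 80% power for sensitivity is:
- 0.85 against 0.78: 236 (power 0.802)
- 0.78 against 0.85: 251
- 0.85 against 0.92: 169

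So 236, which the article prints under Prognosis of ATE, comes out of a calculation for sensitivity alone, and 240 is close to it (power 0.794). Specificity first reaches 80% at 335 (0.68 against 0.75) or 278 (0.75 against 0.82). Two-sided, no direction of the 0.07 difference brings specificity to 80% at 240.

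**Power at 240 per class, in the two readings where rejection supports the test.** At a locked cut-off, sensitivity is estimated in ATE subjects and specificity in no-ATE subjects. These are different people, so joint power is the product.

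| Null (Se/Sp) | Truth (Se/Sp) | c (Se/Sp) | Se power | Sp power | Joint |
|---|---|---|---|---|---|
| 0.78/0.68 | 0.85/0.75 | 200/178 | 0.794 | 0.649 | 0.794 × 0.649 = 0.516 |
| 0.85/0.75 | 0.92/0.82 | 215/194 | 0.9285 | 0.7146 | 0.9285 × 0.7146 = 0.663 |

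**Separating the two causes.** Specificity alone is already below 0.80, at 0.649 or 0.715. The joint requirement takes off a further 0.649 − 0.516 = 0.133 in the first reading and 0.715 − 0.663 = 0.052 in the second. If each test had exactly 80% power, the joint power would be 0.80 × 0.80 = 0.64.

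**Sensitivity to the reading.** Over all 16 two-sided combinations of direction for the two measures, the product runs from 0.516 to 0.693. A one-sided 0.05 test, which the text does not specify, gives 0.631 and 0.777 for the two readings above.

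**What the planned validation cohort would give.** 786 × 0.50 = 393 per class.
- Nulls 0.78/0.68: 0.946 × 0.859 = 0.813
- Nulls 0.85/0.75: 0.990 × 0.919 = 0.910

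With 5% loss (about 373 per class), the first reading gives 0.934 × 0.838 = 0.783. With 10% loss (about 354), it gives 0.917 × 0.806 = 0.739.

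**The case against.** The strongest reply is that no joint success rule is printed. The article writes two separate hypotheses and quotes 0.80 for a one-sample test, not for a joint claim. The 85% and 75% minimum governs the choice of cut-off in training, and a formal rule may sit in a document not shown. This stands in part. The joint rule is an inference, though a strong one, since both measures are called essential and each has a minimum at the same cut-off. It does not rescue the 0.80, because specificity taken alone has only 0.65 to 0.71 power at 240 in these two readings.

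Three stronger readings are tempting, and the documents do not support them:

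- **A third joint figure of 53%.** With nulls 0.85/0.75 and truth 0.78/0.68, the product is 0.794 × 0.674 = 0.535. That is the chance of showing both measures deficient. It is not power for the diagnostic claim, even though this direction is the one that reproduces 236.
- **The whole gap as a joint-power effect.** The distance of 14 to 28 points below 80% mixes the specificity shortfall with the joint requirement. The latter alone accounts for 80% falling to 64%.
- **The same shortfall in prognosis.** At 236 and 157 subjects the same products would be 35% to 48%. Prognosis of ATE, however, refers to prevalence, confidence intervals and error and does not tie those sizes to this joint test. The figures would hold only if the test were applied there.

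**Conclusion.** The point holds. The stated 0.80 is met, approximately, for sensitivity only. Specificity has 0.65 to 0.71 power at 240 no-ATE subjects, and power to meet both criteria is 52% or 66%, depending on whether 0.85/0.75 are the true values or the nulls.

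This rests on four assumptions: exact two-sided tests at 0.05, true values exactly 0.07 above the null, a cut-off fixed before validation, and a requirement that both criteria be met. Without the last, the joint figures fall away but the specificity shortfall remains. If 0.85/0.75 were meant as both the null and the true values, no power figure would apply, which is a further reason to state both. The diagnostic validation size should be revised, but the study need not be enlarged.

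**What to change.** In Sample Size Estimation:
- State the null and the alternative for sensitivity and for specificity, and the direction of the 0.07 difference.
- State that diagnostic validation succeeds only if both criteria are met. Each test keeps the full α, because a claim that requires both needs no split.
- Replace the single 0.80 with the two separate powers and their product at the actual evaluable numbers.

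In Diagnosis of ATE, replace the 240 cap for the validation phase so that all evaluable subjects of the 786-subject validation cohort are used, as the subject-sharing text permits. Report power for the number expected to be evaluable: 393 per class allows for no attrition, and under nulls 0.78/0.68 the joint power drops below 80% at 5% loss.

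The cost is rewording and, if 240 per class is kept, a less favourable stated power. No added enrolment is needed, since the article already plans blood samples, cognitive testing and adjudication for these subjects.

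### The sensitivity and specificity hypotheses are two-sided tests of equality to the desired values, with null and alternative values unassigned, so they do not test whether the 85%/75% minimum is met

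*Protocol article*

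**What the plan says.** All references are to the protocol article.

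- **Sample Size Estimation, hypotheses.** The null hypotheses are Se = Se0 and Sp = Sp0 and the alternatives are Se ≠ Se0 and Sp ≠ Sp0. The text presents these as the hypotheses to be tested. It adds that "Se_0_ is the desired sensitivity and Sp_0_ is the desired specificity".
- **Sample Size Estimation, inputs.** The assumptions are "a clinical sensitivity of 0.85 and specificity of 0.75", "a “difference to detect” of 0.07", and "alpha of 0.05 and a power of 0.80". The text also says "The sample size is based on the binomial test for a one sample design using a two-sided significance level of α = 0.05". The null value p0 and alternative p1 are defined only generically. Neither 0.85/0.75 nor the 0.07 shift is assigned to one or the other, and the shift has no stated direction.
- **Sample Size Estimation, decision rule.** "If m ≥ c, then the null hypothesis is rejected at α significance level", where m is the number of observed outcomes of interest.
- **Diagnosis of ATE.** In training there is "a threshold selected to ensure the model meets the minimum sensitivity and specificity of 85 and 75%, respectively, with confidence intervals". The model is then tested in an independent validation cohort, and p-values for sensitivity and specificity are reported. Each of the two classes is capped at 240 evaluable subjects, and validation needs the same total of 480. Algorithm Training and Testing uses the same 85%/75% minimum for both the diagnostic and the prognostic thresholds.
- **Prognosis of ATE.** 236 high-risk and 157 comparison subjects are needed. At 50% ATE prevalence this means 786 blunt head trauma subjects for training and another 786 for validation.

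**The concern.** The study asks whether performance is at least an acceptable minimum. A two-sided test of equality to the desired value answers another question: whether performance differs from that value in either direction. If the BRAINBox test works as hoped, the null is true and a non-significant result is expected. A significant result may be good or bad news. A non-significant result does not establish that 85%/75% is met.

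The two-sided alternative also sits beside a rule that rejects only for large m, and the reader cannot tell which value is p0 and which is p1. The stated 80% power therefore has no clear link to the claim the validation cohort is meant to support.

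**Working it through.** **Inputs.** n = 240 per class (Diagnosis of ATE); 236 and 157 (Prognosis of ATE); 0.85, 0.75, shift 0.07, two-sided α = 0.05, power 0.80 (Sample Size Estimation). All tails are exact binomial with at most 0.025 in each, X ~ Bin(n, p). Sensitivity and specificity come from different subjects, so joint probabilities are products.

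**1. Reproducing the planned number.** Find the first n at which the power of the two-sided exact test reaches 0.80.

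| p0 vs p1 | first n |
|---|---|
| Se 0.85 vs 0.78 | 236 |
| Se 0.78 vs 0.85 | 251 |
| Se 0.85 vs 0.92 | 169 |
| Sp 0.75 vs 0.82 | 278 |
| Sp 0.75 vs 0.68 | 324 |
| Sp 0.68 vs 0.75 | 335 |

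The first row matches the prognostic 236 exactly: at n = 236 the lower rejection region is X ≤ 189, and P(X ≤ 189 | 0.78) = 0.802. At n = 240 the same test has power 0.794. The match is to the first n that reaches 0.80. The article's own definition, power at or above 0.80 for every larger n, would give 255. No two-sided specificity variant gives 240.

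The number that reproduces is thus the one for detecting sensitivity falling from 0.85 to 0.78.

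**2. What the stated test does at n = 240, with p0 = 0.85/0.75.**

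- Se: reject if X ≤ 192 (80.0%) or X ≥ 215 (89.6%).
- Sp: reject if X ≤ 166 (69.2%) or X ≥ 194 (80.8%).

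| Truth | Rejects low | Rejects high | Total |
|---|---|---|---|
| Se 0.85 | 0.0218 | 0.0248 | 0.0466 |
| Sp 0.75 | 0.0239 | 0.0199 | 0.0438 |
| Se 0.78 | 0.794 | <0.001 | 0.794 |
| Sp 0.68 | 0.674 | <0.001 | 0.674 |
| Se 0.92 | <0.001 | 0.928 | 0.928 |
| Sp 0.82 | <0.001 | 0.715 | 0.715 |

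If both are exactly as desired, the chance of rejecting upward on both is 0.0248 × 0.0199 ≈ 0.0005.

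**3. The printed inequality.** Taken literally, the null sum from c to n need only be ≤ 1 − α/2. At n = 240 and p0 = 0.85 the smallest such c is 194, and P(X ≥ 194 | 0.85) = 0.968, so rejecting for m ≥ c would reject a true null 96.8% of the time. It is treated here as a misprint.

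**4. Power of a directional rule.** Success means that the lower limits of both two-sided 95% exact intervals exceed their floors, which is the upper-tail test at one-sided 0.025.

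| n (Se / Sp) | Floors 0.85/0.75, truth 0.92/0.82 | Floors 0.78/0.68, truth 0.85/0.75 |
|---|---|---|
| 240 / 240 | 0.928 × 0.715 = 0.66 | 0.794 × 0.649 = 0.52 |
| 393 / 393 | 0.990 × 0.919 = 0.91 | 0.946 × 0.859 = 0.81 |
| 236 / 157 (prognosis) | 0.908 × 0.529 = 0.48 | 0.775 × 0.451 = 0.35 |

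The 393 per class is 786 × 0.50, the validation enrolment already planned for prognosis.

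**The case against.** **Se0 = 0.85 is never stated.** True. The 0.85/0.75 values are described as assumptions drawn from the pilot trial, which could make them the expected truth, and a null of 0.78 against 0.85 also has power 0.794 at n = 240. The word for the null value, the 85%/75% minimum and the exact match at 236 favour 0.85 as the null. If 0.78 was meant, calling it the desired value is wrong, and the section still needs correcting.

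**Favourable results can demonstrate the minimum.** A reader might infer that no outcome could. The article does not support that. With the null at 0.85/0.75, at least 215/240 and 194/240 would show both minimums exceeded, each at one-sided 0.025. So would confidence intervals lying wholly above 0.85/0.75, and intervals are to be reported. The upper-tail rejection rule points the same way.

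**Non-rejection is not called success.** Correct. A reader might go on to compute how often an inferior test would pass by not rejecting, but the article gives no such rule, so those pass rates are not relied on here.

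**Performance need not sit exactly at 85%/75%.** Also correct: the training threshold must meet a minimum, not equal it. The 4.7% and 4.4% describe the boundary case only.

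**A condensed article may leave the success criterion elsewhere.** That excuses a missing criterion. It does not excuse printed hypotheses that conflict with the stated aim and with the printed rejection rule.

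**Conclusion.** The point holds in this form: the printed hypotheses are non-directional, sit beside an upper-tail rule, do not assign 0.85/0.75 and the 0.07 shift to null and alternative, and do not match an aim expressed as a minimum. On the reading that Se0/Sp0 = 0.85/0.75, with n = 240 per class and exact tails:

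- a test exactly at the desired values rejects 4.7% (Se) and 4.4% (Sp) of the time;
- a true sensitivity of 0.78 leads to rejection 79% of the time, for the wrong reason from the sponsor's viewpoint;
- the reproduced 236 gives power to detect a shortfall, not power to validate;
- only performance well above 0.85/0.75 would demonstrate the minimum.

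This affects the primary performance claim and should be corrected before validation. It does not mean that the data could never support the claim.

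**What to change.** Before validation data are unblinded:

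1. Replace the hypotheses with H0: Se ≤ Se floor or Sp ≤ Sp floor, against Ha: both exceed their floors. Success means that the lower limits of both two-sided 95% exact intervals exceed their floors. Both must be met, so alpha need not be split.
2. State which values are the floors and which the assumed truth. If 85%/75% is truly the minimum, the floors are 0.85/0.75, and the assumed truth must lie above them (0.92/0.82 with the stated shift). Floors of 0.78/0.68 suit an assumed truth of 0.85/0.75 but would not demonstrate the 85%/75% minimum.
3. Correct the printed inequalities and the decision rule to match.
4. Restate power for sensitivity and specificity, separately and jointly.

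**Cost.** This goes beyond rewording. At 240 per class, joint power is about 0.66 (floors 0.85/0.75) or 0.52 (floors 0.78/0.68). For diagnosis, lifting the 240 cap and analysing all 786 planned validation subjects gives about 0.91 or 0.81 with no added enrolment, provided prevalence is near 50% and all 786 are evaluable. For prognosis, 236 and 157 subjects give only about 0.48 or 0.35. The article should say so, or the sponsor should revisit those numbers.

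### The printed inequalities for the exact binomial critical value do not define a test at the stated alpha, contradict the stated power, and give only one tail of a two-sided test

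*Protocol article*

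**What the plan says.** The section Sample Size Estimation of the protocol article names a one-sample binomial test with "a clinical sensitivity of 0.85 and specificity of 0.75", "a “difference to detect” of 0.07" and a "two-sided significance level of α = 0.05 and a power of 1-β = 0.80". The null hypotheses are Se = Se0 and Sp = Sp0, and the alternatives are two-sided (≠).

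With p0 the null value, p1 the alternative, n the sample size and m the observed count, the section then defines a critical value c by two sums from i = c to n:

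- under p0, the sum ends in "p_{0}^{i}{\left(1-p_{0}\right)}^{n-i}\leq 1-\alpha /2";
- under p1, the sum ends in "p_{1}^{i}{\left(1-p_{1}\right)}^{n-i}\leq 1-\beta".

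The rule follows: if m is at least c, "then the null hypothesis is rejected at α significance level". The next sentence defines N as the sample size from which power never falls below 1−β.

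The section Diagnosis of ATE says that the sample size was calculated in PASS. It caps each of the ATE and no-ATE cohorts at 240 evaluable subjects and asks for an equal number for validation. The section Prognosis of ATE gives 236 evaluable subjects with the target condition.

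**The concern.** The sum from c to n under p0 is the probability, when the null is true, of landing in the rejection region m ≥ c. For a two-sided test at α = 0.05 that probability must be at most 0.025 in the upper tail. The display allows up to 0.975.

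The same sum under p1 is the power of that rule. The display caps it at 0.80, and the text directly after requires at least 0.80. Both cannot be right.

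An alternative of ≠ needs a lower rejection region as well, and none is given.

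This is the only rejection rule in the article for hypotheses that it says will be tested. Anyone who applied it literally to the validation counts could obtain a test with a size far from 5%. They would also not know whether rejection means that performance is above or below the target.

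**Working it through.** **Inputs.** From Sample Size Estimation: p0 = 0.85 (sensitivity) and 0.75 (specificity); difference 0.07, direction not given; α = 0.05 two-sided, so α/2 = 0.025 and 1−α/2 = 0.975; 1−β = 0.80. From Diagnosis of ATE: n = 240 per cohort. From Prognosis of ATE: n = 236. All tails are exact: P(X ≥ c | p) = Σ (i = c to n) C(n,i) pⁱ(1−p)ⁿ⁻ⁱ.

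**1. The plan's own figure.** A correct two-sided exact test of 0.85 against 0.78 first reaches 80% power at n = 236. Rejecting in the lower tail at m < 190 gives P(X < 190 | 0.85) = 0.0246 and P(X < 190 | 0.78) = 0.802. This matches 236 exactly and is close to 240 (at n = 240 the rule is m < 193, with power 0.794). The 240 is not reproduced for specificity: 0.75 needs 278 against 0.82, or 324 against 0.68. That is a separate matter from this point.

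**2. The printed pair with p1 = p0 − 0.07, n = 240.** Smallest c that meets both printed inequalities:

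| | c | P(X ≥ c given p0), printed bound 0.975 | P(X ≥ c given p1), printed bound 0.80 |
|---|---|---|---|
| Sensitivity, 0.85 vs 0.78 | 194 (80.8%) | 0.968 | 0.163 |
| Specificity, 0.75 vs 0.68 | 168 (70.0%) | 0.967 | 0.278 |

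Both printed conditions hold, yet the rule rejects a true null about 97% of the time.

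**3. The printed pair with p1 = p0 + 0.07, n = 240.** Now the second inequality forces c upward. Smallest c that meets both:

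| | c | Size | Power |
|---|---|---|---|
| Sensitivity, 0.85 vs 0.92 | 218 | 0.005 | 0.788 |
| Specificity, 0.75 vs 0.82 | 193 | 0.029 | 0.768 |

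Power cannot exceed 0.80 here because the inequality forbids it. For specificity the upper-tail size is also above 0.025.

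**4. c is not fixed.** Both conditions are ceilings, and both tails shrink as c grows, so every larger c also satisfies them. The values above are the smallest that qualify, and the text does not say to take the smallest.

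**5. Two repairs that give valid tests.**

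- *Upper tail:* P(X ≥ c | p0) ≤ α/2, reject at m ≥ c. At n = 240, c = 215 for 0.85 (size 0.0248, power 0.928 at 0.92) and c = 194 for 0.75 (size 0.0199, power 0.715 at 0.82). These c values come from the size condition alone. The 194 here is for specificity and only coincides with the 194 in step 2.
- *Lower tail:* P(X ≥ c | p0) ≥ 1−α/2, reject at m < c. At n = 236, 0.85 against 0.78, this is the m < 190 rule of step 1.

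With both tails at n = 236 and p0 = 0.85, the rule is m < 190 or m ≥ 212, with total size 0.0246 + 0.0196 = 0.0442.

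**The case against.** A reader might infer that the trial's type I error is near 97%. The article does not support that as a general statement. It says that the two conditions are solved together, and a rule that rejects for high counts suggests p1 above p0. In that case the size is 0.005 or 0.029, not 0.97. The 97% arises only at the smallest c with p1 below p0, or if the second inequality is ignored. What stands is that the pair does not define a valid c in either direction.

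A reader might also take the display as the declared decision rule for validation. It sits under Sample Size Estimation and is introduced as a way to find N. The validation reporting in Diagnosis of ATE speaks of confidence intervals, predictive values and p-values, and nowhere says that c will be applied to the validation counts. This objection stands in part: the section does say that the hypotheses will be tested, and it prints no other rejection rule.

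A third inference would be that the sample size is wrong because of these inequalities. The article attributes the calculation to PASS, and 236 follows from a correct exact test.

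Finally, the display may be a garbled lower-tail rule, since 1−α/2 is the right bound if the first inequality is reversed and rejection is at m < c. That reading fits 236. It does not rescue the text, because the inequality and the rejection direction would then both be wrong. It does mean that an upper-tail correction cannot simply be assumed.

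**Conclusion.** The display is wrong as written. Its bound on the rejection region is 1−α/2 where a rule of m ≥ c needs α/2. Its power inequality contradicts the power promised in the text that follows. It supplies one tail for a two-sided alternative.

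Its size cannot be given as one number, because the direction of the 0.07 difference is not stated. At n = 240 the literal rule has a null rejection probability of about 0.97 in one direction and power of 0.788 (sensitivity) or 0.768 (specificity) in the other. These figures assume n = 240 evaluable subjects per cohort, the smallest c that meets both printed conditions, and the stated 0.85, 0.75 and 0.07.

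This is an error in the written rule, not a demonstrated error in the sample size or in an analysis already run. Harm would follow only if the validation test were carried out from this text.

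**What to change.** 1. State p1 and its direction for sensitivity and for specificity, and say which tail counts as success.
2. Print the inequalities that match:
   - upper tail: P(X ≥ c | p0) ≤ α/2 and P(X ≥ c | p1) ≥ 1−β, reject at m ≥ c; or
   - lower tail: P(X ≥ c | p0) ≥ 1−α/2 and P(X < c | p1) ≥ 1−β, reject at m < c.
3. If the test stays two-sided, give both critical values for each endpoint.
4. Recompute the critical values for the actual number of evaluable validation subjects, and fix them before the validation data are tested.

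The cost is a text correction and a short exact-binomial calculation, with no change to enrolment or data collection from this point alone.

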### Prognosis of ATE

A separate model will be fit for symptoms at each post-enrollment time point, with data evaluated during the modeling phase, to determine the prognostic output report. Results will be grouped into low and high risk. Based on the data from the modeling/training phase, the symptom categories that are statistically supported, with sufficient prevalence to make a justified prognostic claim, will be reported. If applicable, symptoms categories may be combined into one overarching composite result, and defined as either low or high risk. Data handling for modeling will be the same as the diagnostic analysis, with the models identifying the likelihood that a subject will experience ATE symptoms at 14, 30, and 90 days.

Sample size for TBI subjects adjudicated as high or low risk for ATE symptoms at 14, 30 and 90-days post-injury is based on estimated prevalence of 60% of subjects having unresolved or emergent injury-related symptoms in the suspected ATE population at each time point (30). Using published and internal information on prevalence, as well as predefined sensitivity, specificity, confidence intervals, error, the total number of ATE subjects needed was calculated. The number of subjects with high risk of outcomes needed, the target condition for the prognosis, will be 236 evaluable subjects. The number of subjects without ATE will be 157, yielding a total number of subjects of 393 for algorithm training. With the estimated prevalence of ATE being 50%, a total of 786 blunt head trauma subjects is needed for algorithm training. This study design uses the same sample sizes for both training and validation phases, just as in the diagnostic models. Therefore, the same number of blunt head trauma subjects (*n* = 786) are needed for validation. To provide sufficient data for prognosis modeling in training and validation cohorts, up to 1,600 suspected ATE subjects will be needed. Enrollment numbers are subject to increase or decrease pending on true prevalence, results of data analysis and/or attrition.

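### The prognostic figure of 236 appears to be only the first sample size to reach 80% power, not the size from which power stays there, as the article defines N; on the reading that reproduces 236, that N is 255

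*Protocol article*

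**What the plan says.** All references are to the protocol article.

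- **Sample Size Estimation, test and error rates:** "The sample size is based on the binomial test for a one sample design using a two-sided significance level of α = 0.05", with power 0.80.
- **Sample Size Estimation, assumptions:** "a clinical sensitivity of 0.85 and specificity of 0.75" and "a “difference to detect” of 0.07". The direction of the difference is not given. The null value is described as the desired sensitivity or specificity.
- **Sample Size Estimation, definition of N:** N is the smallest size such that, for any n at or above it, "the power is always greater than or equal to 1-β". The article calls this N the exact binomial sample size.
- **Prognosis of ATE:** the number with the target condition "will be 236 evaluable subjects". The 60% symptom prevalence turns this into 393 subjects, the 50% ATE prevalence into 786 per phase, and the two phases into up to 1,600.
- **Diagnosis of ATE:** the two cohorts "should each not exceed 240, which makes the total number of evaluable subjects 480".

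The article does not state the power achieved at 236 or at 240.

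**The concern.** An exact binomial test has a whole-number critical value. When n rises by one and the critical value does not move, power falls; when the critical value moves, power rises. There are therefore two candidate sample sizes: the first n that reaches 80%, and the larger n from which power never drops below 80% again. The article's definition is the second. If 236 is the first, the text attaches a guarantee to a number that does not carry it.

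The guarantee is useful in this study because the number of subjects with the target condition is not fixed by design. It depends on adjudication, prevalence and attrition, and the article itself says that enrolment may move with these. A reader who relies on the definition would believe that any count above 236 secures 80% power for sensitivity.

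**Working it through.** **Inputs.** Two-sided alpha 0.05, power 0.80, sensitivity 0.85 and difference 0.07 come from Sample Size Estimation. The prevalences of 60% and 50% come from Prognosis of ATE. Two assumptions are needed: p0 = 0.85 with p1 = 0.78, and alpha split as 0.025 in each tail.

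**Formula.** For each n, let c_L be the largest x with P(X ≤ x | n, p0) ≤ 0.025, and c_U the smallest x with P(X ≥ x | n, p0) ≤ 0.025. Power is P(X ≤ c_L | n, p1) + P(X ≥ c_U | n, p1). For p1 = 0.78 the second term is negligible.

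**Step 1: reproduce 236.** At n = 235 power is 79.2%. At n = 236 the test rejects at 189 or fewer positives, the lower-tail size is 0.0246 and power is 80.2%. No smaller n reaches 80%, so 236 is reproduced exactly, as the first crossing.

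**Step 2: check the article's definition of N.**

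| n | Lower critical value | Power |
|---|---|---|
| 236 | 189 | 80.2% |
| 237 | 189 | 76.4% |
| 240 | 192 | 79.4% |
| 243 | 194 | 77.7% |
| 248 | 198 | 77.9% |
| 254 | 203 | 79.1% |
| 255 | 204 | 80.0% |

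Power is below 80% at 237–240, 243–245, 248–250 and 254, which is 11 of the 19 sizes from 236 to 254. From 255 it stays at or above 80% for every n checked (up to 899). The N that meets the definition is therefore 255.

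**Step 3: other directions and conventions.**

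| Null vs alternative, test | First n at 80% | N by the article's definition |
|---|---|---|
| 0.85 vs 0.78, equal-tail exact | 236 | 255 |
| 0.78 vs 0.85, equal-tail exact | 251 | 266 |
| 0.85 vs 0.92, equal-tail exact | 169 | 185 |
| 0.92 vs 0.85, equal-tail exact | 156 | 170 |
| 0.85 vs 0.78, one-sided exact | 188 | 208 |
| 0.85 vs 0.78, minimum-likelihood exact | 222 | 251 |
| 0.85 vs 0.78, score | 212 | 232 |
| 0.85 vs 0.78, Wald | 255 | 275 |

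The figure 236 appears once, as the first crossing in the first row. It never appears in the last column.

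**Step 4: expected power when the number of positives is random.** Let the positives among 393 subjects be Binomial(393, 0.60). Expected power is the sum over n of P(n) × power(n), which gives 78.0%. The central 95% range of n is 217 to 255. Over those sizes power runs from 72.3% (n = 219) to 82.5% (n = 253).

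**Step 5: the enrolment chain.** As stated: 236 / 0.60 = 393; 393 / 0.50 = 786; 786 × 2 = 1,572, within 1,600. With 255: 255 / 0.60 = 425; 425 / 0.50 = 850; 850 × 2 = 1,700. With 266: 266 / 0.60 = 443.3, rounded up to 444; then 888 and 1,776.

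**The case against.** The strongest objection is that the direction is inferred. The printed rule rejects when the count is at or above a critical value, and the null is the desired value. Taken literally, that suggests 0.85 against 0.92. On that reading the N of the definition is 185, power at 240 is 92.9%, and both 236 and 240 satisfy the guarantee. This stands as a caveat: 255 cannot be read off the text without an assumption. However, 0.85 against 0.92 cannot be the source of 236, whereas 0.85 against 0.78 gives it to the unit.

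Second, the link between 236 and the definition is itself an inference. The definition is introduced for the primary endpoint, and Prognosis of ATE describes its calculation only in general terms. The value 240 is a ceiling and is never called N. This also stands, although the article describes no other sample size method.

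Third, the value 255 depends on the two-sided convention: minimum-likelihood gives 251, and a score test gives 232, at which 236 would comply. Neither convention produces 236.

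Fourth, the 78% expected power is not due to the sawtooth alone. About half of the likely counts fall below 236, and that would reduce average power even if power rose smoothly with n. Moving to 425 subjects would likewise leave about half of the counts below 255. The figure describes the design fairly, but it does not measure the wording error.

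Finally, the loss is small: 0.6 percentage points at 240 and about 2 points on average.

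**Conclusion.** The point holds as a minor inconsistency between a stated property and the number used. Assuming 0.85 (null) against 0.78 with an equal-tail exact test, 236 is the smallest n reaching 80% power (80.2%), not the N that the article defines, which is 255. With null and alternative swapped the gap is wider: N is 266 and power at 236 is 77.5%. The finding concerns sensitivity only.

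A reader might infer three stronger things that the document does not support:

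- **That the article's text alone fixes N at 255.** It does not, because the direction of the 0.07 difference and the tail convention are unstated.
- **That 240 sits at a low point of the power curve.** The low point is 237. At 240 power is climbing back and misses 80% by 0.6 points, and 240 is a cap.
- **That the planned enrolment is inadequate.** Both 1,700 and 1,776 exceed the planned 1,600, but the article allows enrolment to change and sets a maximum of 2,000 blunt head trauma subjects, which covers both.

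**What to change.** State p0, p1, the direction of the 0.07 difference and the two-sided convention. Then choose one of two corrections.

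1. **Keep 236.** Describe it as the smallest n that reaches 80% power and delete the claim that power stays there at every larger size. Give the power at 240 as 79.4%. Give expected power as about 78% when the number of positives is Binomial(393, 0.60), with about 72–82% over the likely sizes of 217 to 255. This changes text only and needs no extra enrolment.
2. **Keep the definition.** Restate N as 255 and the chain as 425, 850 and 1,700. This adds 100 to the planned 1,600 and stays within the 2,000 maximum.

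The first option is the cheaper and is sufficient.
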